#### Provisions for post-trial care {30}

There are no provisions for post-trial care given the anticipated low risk of harm from a participant’s involvement in this trial [18, 19]. At the end of the trial, participants will return to the standard care according to the medical indication and current guidelines.

### Outcomes {12}

The primary outcome of the study is the difference between the Exp group and Ctrl group in functional mobility of the UL. It will be measured using the Fugl-Meyer Assessment Scale for Upper Extremity (FMA-UE).

Secondly, we will investigate clinical, kinematic and neurophysiological changes between the two groups using:The Box and Block Test to assess manual dexterity.The Modified Ashworth Scale to assess spasticity.Kinematics variables, recorded via inertial measurement units and motion analysis during three-reaching tasks and the Box-and-Block test, to assess functional movements.TMS-evoked potentials, recorded via TMS-EEG, to assess cortical reactivity.TRSP, recorded via TMS-EEG, to assess oscillatory dynamics of the PPC and M1.PLV, recorded via TMS-EEG, to assess the actual connectivity between a targeted area with respect to the entire neural network.

### Participant timeline {13}

After screening, all patients will be tested for motor (FMA) and cognitive function (MMSE). If eligible for the study, their evaluation will be completed in 72 h before they start the experimental treatment. After evaluation, each patient will perform the 3 weeks of treatment. During the 72 h, after the last session, we will perform the post-treatment evaluation. The follow-up evaluation will be performed 28 days after the end of the treatment with a 3-day margin of tolerance. The complete treatment and assessment phases are available in Fig. 3.

**Fig. 3 Fig3:**
[figure not shown]
Complete treatment and assessment phases

### Sample size {14}

According to an a priori Power analysis, considering 80% power and a 95% CI, 32 patients would be needed for necessary sample size, based on previously published work on cortical plastic changes induced by neurostimulation via TMS [14].

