**Methods:**

A randomised double-blind controlled trial design involving 32 patients with a single chronic stroke (onset > 180 days) was planned. Each patient will undergo 15 consecutive sessions (5 days for 3 weeks) of paired associative stimulation (PAS) coupled with UL robot-assisted therapy. PAS stimulation will be administered using a bifocal transcranial magnetic stimulator (TMS) on the posterior-parietal cortex and the primary motor area (real or sham) of the lesioned hemisphere. Clinical, kinematics and neurophysiological changes will be evaluated at the end of protocol and at 1-month follow-up and compared with baseline. The Fugl-Meyer assessment scale will be the primary outcome. Secondly, kinematic variables will be recorded during the box-and-block test and reaching tasks using video analysis and inertial sensors. Single pulse TMS and electroencephalography will be used to investigate the changes in local cortical reactivity and in the interconnected areas.

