### Recruitment {15}

We will screen subjects admitted to the hospital until the target population is achieved (32 subjects). In case of heterogeneity of demographic characteristics between the two groups of study, the screening may continue after the anticipated sample size.

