#### Plans to promote participant retention and complete follow-up {18b}

To promote retention, we planned a short-time follow-up (4 weeks) to maximise the completeness of data collection. In this way, we hypothesise a low number of non-retention cases (< 20%).

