### Statistical methods

#### Statistical methods for primary and secondary outcomes {20a}

Data characterised by normal distribution will be expressed as means with standard deviations. Parameters not normally distributed will be expressed as medians with the interquartile ranges. Parametric data will be analysed with a 3 × 2 mixed model ANOVA considering time (TIME: T0 vs T1 vs T2) and group allocation (GROUP: Real vs Ctrl) as within and between factors, respectively, with *α* = 0.05. Each significant interaction (TIME × GROUP) will be further explored with the Bonferroni post hoc correction. Nonparametric data will be investigated with Friedman’s test and, if *p* < 0.05, with Wilcoxon test such as post hoc. Correlations (Pearson for normal distributed data or Spearman for non-normal distributed data) and regression analysis will be performed between clinical, kinematic and neurophysiological data to investigate casual and causal interaction respectively. Sub-group analysis can be performed after severity stratification (i.e. FMA < 17).

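### The 80% power quoted for 32 patients is not shown to apply to the FMA-UE primary outcome, and 32 carries no visible allowance for the losses the protocol allows for

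*Protocol article*

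**What the plan says.** Section {14} (Sample size) is a single sentence, which fixes the number by "considering 80% power and a 95% CI, 32 patients would be needed for necessary sample size". The only support it offers is a citation to reference 14, and it describes the calculation as "based on previously published work on cortical plastic changes induced by neurostimulation via TMS". It names no outcome, difference, SD, correlation or test.

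The abstract says "The Fugl-Meyer assessment scale will be the primary outcome", and section {12} (Outcomes) confirms it. Section {12} lists the cortical measures taken with TMS-EEG (evoked potentials, spectral perturbation, phase locking) among the secondary outcomes.

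Section {15} (Recruitment) says "We will screen subjects admitted to the hospital until the target population is achieved (32 subjects"). It permits recruitment beyond that number only if the groups differ demographically, not to replace losses. In section {18b} (retention) the investigators write "we hypothesise a low number of non-retention cases" and put the figure below 20%. Section {20c} plans multiple imputation for missing values. Section {20a} plans a 3 × 2 mixed ANOVA (time by group) with alpha of 0.05.

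**The concern.** The only basis given for the number of patients is described in terms of cortical plasticity, which in this trial belongs to the secondary outcomes. Nothing connects the 80% to a difference in FMA-UE. A reader who meets a null FMA-UE result will take it as coming from a trial with 80% power for that outcome, and the text does not support that reading.

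The second part is internal to the article. Section {14} says that 32 patients are needed, section {15} stops recruitment at 32, and section {18b} allows for up to a fifth not being retained. If the needed number means evaluable patients, these three statements do not fit together.

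**Working it through.** **Reproducing the stated figure.** This is not possible, because no effect size, SD, correlation or test is given. The 32 can be neither confirmed nor refuted. The check therefore runs backwards, from 32 to the effect it can detect.

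**Inputs from the protocol.** Power 80% and N = 32 ({14}); alpha 0.05 ({20a}); recruitment target 32 ({15}); losses below 20% ({18b}).

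**Assumptions.** 1:1 allocation (16 per arm), a two-sided test, and complete cases after losses. The protocol states neither the ratio nor the sidedness.

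**Step 1: detectable difference with 32.** Two-sample t-test, noncentral t, noncentrality d·√(n/2), with n per arm and d in SD units.
- n = 16: 80% power at d = 1.02.
- Check by normal approximation: (1.96 + 0.84) × √(2/16) = 0.99.

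**Step 2: losses.** Take the effect that gives exactly 80% with 16 per arm (d = 1.02) and reduce n.

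| Loss | Patients left | Per arm | Power |
|---|---|---|---|
| 0% | 32 | 16 | 80% |
| 5% | 30.4 | 15.2 | 78% |
| 10% | 28.8 | 14.4 | 75% |
| 20% | 25.6, taken as 26 | 13 | 71% |

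The time-by-group F test of a 2 × 3 repeated-measures ANOVA (sphericity assumed) gives about 70% at N = 26, again starting from the effect with 80% power at N = 32. The relative loss is therefore nearly the same under the type of analysis planned in {20a}. Holding 32 evaluable patients at the 20% bound would take 32 / (1 − 0.20) = 40 enrolled.

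**Step 3: does 32 suffice for FMA-UE?** With 13 per arm the unadjusted detectable difference is 1.15 SD. Baseline adjustment multiplies the detectable difference by √(1 − ρ²), where ρ is the correlation between baseline and outcome. The protocol gives no ρ, so two values are assumed.

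| Analysis | Factor | 32 patients | 26 completers |
|---|---|---|---|
| Unadjusted | 1 | 1.02 SD | 1.15 SD |
| Adjusted, ρ = 0.7 | √0.51 = 0.714 | 0.73 SD | 0.82 SD |
| Adjusted, ρ = 0.9 | √0.19 = 0.436 | 0.45 SD | 0.50 SD |

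The detectable difference varies more than twofold with the analysis and the correlation, and the protocol fixes no FMA-UE target against which to judge it.

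**The case against.** Four points can be made for the protocol.

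- **The source of the effect size is not visible.** The mention of cortical plastic changes describes the cited work as a whole. The Background section cites the same reference for neurostimulation combined with neurorehabilitation, so a clinical outcome from that source is not excluded. This stands. A reader might infer that the power calculation was done on a neurophysiological outcome and that the 80% is therefore wrong for FMA-UE. The document does not establish that, only that the link to FMA-UE is not shown.
- **A journal article may condense the inputs away.** That is fair as regards a missing SD or test. But the article does state a basis, and the one it states is not described in terms of the primary outcome.
- **The loss figure is a ceiling, and 32 might already include an allowance.** The first half stands: at 5% loss power is still about 78%. On the second half, the text calls 32 the number needed and also makes it the recruitment target, so no allowance can be seen. That is short of proof that losses were ignored.
- **The unadjusted t-test is not the planned analysis.** This also stands. An unadjusted calculation gives only 28% power at 0.5 SD and 59% at 0.8 SD with 16 per arm, and a reader might conclude that the trial is badly underpowered. With baseline adjustment at ρ = 0.9, power at 0.5 SD is 88% with 16 per arm and 80% with 13. The document does not support a claim that 32 is too few.

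The use of a 95% CI to stand for the significance level is loose wording only, since {20a} gives alpha as 0.05.

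**Conclusion.** The concern holds in a limited form. As written, the 80% is not tied to any FMA-UE difference or SD and is not shown to apply to the primary outcome. No arithmetic error is demonstrated.

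If 32 is the number of evaluable patients needed, the recruitment plan does not deliver the stated power once patients are lost: about 75% at 10% loss and about 71% at the 20% bound. These figures rest on the 1:1, two-sided and complete-case assumptions above. Multiple imputation keeps randomised patients in the analysis, but it does not restore the information in outcomes that were never observed.

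Whether 32 is adequate for FMA-UE stays open until a difference, an SD, a correlation and the analysis are stated.

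**What to change.** Keep 32 and rewrite section {14}:

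1. Give the FMA-UE difference detectable with 80% power at two-sided alpha of 0.05, for 32 patients and for 26 completers, under the primary analysis actually used, with the assumed SD and correlation stated.
2. Name the outcome in the cited work that supplied the effect size. If it was not FMA-UE, say that the 80% does not refer to the primary outcome.

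The cost is one rewritten paragraph and a less favourable stated power. No extra patients are needed.

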### Recruitment {15}

We will screen subjects admitted to the hospital until the target population is achieved (32 subjects). In case of heterogeneity of demographic characteristics between the two groups of study, the screening may continue after the anticipated sample size.

### Assignment of interventions: allocation

#### Sequence generation {16a}

A random allocation software for parallel group randomisation will be used to generate a consecutive allocation list.

#### Concealment mechanism {16b}

Allocation concealment will be ensured, the randomisation code will not be generated until the patient has completed all baseline measurements.

#### Implementation {16c}

After the baseline evaluation, the PI or Co-PI requests the allocation to the designated sub-investigator (not involved in the assessment and treatment). The allocation will be revealed exclusively to the neurophysiology technician who will be in charge of performing the stimulation protocol.

### Assignment of interventions: blinding

#### Who will be blinded {17a}

Assessments will be conducted by two assessors blind to treatment allocation. Patients and their caregivers will be instructed during recruitment about the impossibility to receive information about the allocation, even when they explicitly request it.

#### Procedure for unblinding if needed {17b}

Unblinding can be requested and managed by PI only for exceptional circumstances when knowledge of the actual treatment is essential for further management of the patient. In this case, the PI will provide communication with the Clinical Trial Center (CTC) and will include this information in the disseminations.

### Data collection and management

#### Plans for assessment and collection of outcomes {18a}

Clinical, instrumental and neurophysiological evaluation will be assessed at baseline (T0); after the 3 weeks of treatment (T1); and after 7 weeks from the baseline as a follow-up—4 weeks from the end of the treatment—(T2).

Demographics data (i.e. age, gender, lesion site) will be acquired through clinical documentation provided during the screening procedure. All collected data will be stored in an online data sheet protected with a password. To promote data quality, all raters were specifically trained in the administration of the clinical scales and in kinematics evaluation.

##### Clinical and kinematic assessment

A battery of scales and functional tests will be performed to assess functionality of UL as follows: (*i*) the Fugl-Meyer Assessment scale for upper extremity (FMA-UE) for motor-sensory pain and range of motion functions of UL such as primary outcome; (*ii*) the Box and Block test (BBT) for functional mobility (Reaching and grasp/grasp-relax); (*iii*) the Modified Ashworth scale (MAS) for muscle tone function; (*iv*) kinematic assessment of reaching tasks. The FMA-UE is a comprehensive measurement tool for motor function after stroke that was shown to be valid, reliable and responsive to change. The FMA-UE showed excellent inter-rater reliability (ICC of 0.99) and test–retest reliability (ICC = 0.97 for motor score; ICC = 0.81 for sensation, ICC = 0.95 for passive joint motion/pain) [20]. Among other FMA-UE domains, the motor domain is the most widely used, having the primary value of monitoring motor recovery after stroke. Most items in the UL motor domain are based on patient motion, although reflex or resistance must be measured in a few items [21]. The BBT is an instrumented measure of gross manual dexterity, performed by counting the number of blocks that are moved from one compartment of a box to another compartment within 60 s (after 15 s of trial) (Fig. 4A). BBT showed an excellent inter-rater reliability (*r* = 1.00; *r* = 0.99) and test–retest reliability (ICC = 0.97; ICC = 0.96) for the right and left hand, respectively [22, 23]. The MAS is a 6-point clinical measure of muscle spasticity, widely used in neurological patients. MAS showed a good intra-rater reliability (weighted kappa = 0.83) and inter-rater reliability (Kendall’s tau-b = 0.84) [24, 25]. About the reaching task, the patient is sitting in front of a table with the hand on an initial predefined target. The patient is then instructed to reach from the rest position, for three times, a second target signed 30 cm ahead and 30 cm to the midline (Fig. 4B). Both hands will be tested.

**Fig. 4 Fig4:**
[figure not shown]
**A** Box and Block Test. **B** Reaching task

UL linear 3D acceleration and angular velocity will be recorded using inertial measurement units (IMUs). IMU measures are provided with respect to a sensor-embedded frame, generally coinciding with the geometrical axes of the case in which the IMU is housed [26]. This technology can be exploited to obtain UL range of motion and further kinematic features (i.e. functional mobility and activity of daily living tasks) while the patient moves the UL freely [27]. Video analysis is performed by three video cameras placed frontally and sideways (bilaterally) to the subject with an angle of 90°, and then, motion tracking of moving targets will be performed. Both BBT and reaching tasks will be performed with both ULs starting from the unaffected side.

##### Neurophysiological assessment

We will use 120 single pulses for each area (M1 and PPC bilaterally) during electroencephalographic recordings (EEG) to measure changes in the local activity of the stimulated area and on its cortico-cortical connections. The combined use of TMS-EEG represents one of the most promising approaches in the investigation of brain dynamics, in terms of cortical activity and connectivity. Indeed, EEG can record the postsynaptic potentials generated by the TMS-evoked neuronal depolarisation providing direct information on the neurophysiological state of the stimulated area and on its connections over the cortex. Recently, the main components of TEPs that can be detected in the first 200 ms after the probing TMS pulse have been put in relation with the activity of GABAergic interneurons [28].

#### Plans to promote participant retention and complete follow-up {18b}

To promote retention, we planned a short-time follow-up (4 weeks) to maximise the completeness of data collection. In this way, we hypothesise a low number of non-retention cases (< 20%).

#### Data management {19}

All data are collected electronically through an interface that complies with European (GDPR No. 679/2016) and Italian (D.L. 101/2018) data protection guidelines. Personal data and contacts will be recorded in a separate dataset and identified via an alpha-numeric ID.

#### Confidentiality {27}

To ensure privacy, an alpha-numeric ID for each patient will be assigned to preserve personal information and contacts.

#### Plans for collection, laboratory evaluation and storage of biological specimens for genetic or molecular analysis in this trial/future use {33}

No biological specimens will be collected in the present study.

### Statistical methods

#### Statistical methods for primary and secondary outcomes {20a}

Data characterised by normal distribution will be expressed as means with standard deviations. Parameters not normally distributed will be expressed as medians with the interquartile ranges. Parametric data will be analysed with a 3 × 2 mixed model ANOVA considering time (TIME: T0 vs T1 vs T2) and group allocation (GROUP: Real vs Ctrl) as within and between factors, respectively, with *α* = 0.05. Each significant interaction (TIME × GROUP) will be further explored with the Bonferroni post hoc correction. Nonparametric data will be investigated with Friedman’s test and, if *p* < 0.05, with Wilcoxon test such as post hoc. Correlations (Pearson for normal distributed data or Spearman for non-normal distributed data) and regression analysis will be performed between clinical, kinematic and neurophysiological data to investigate casual and causal interaction respectively. Sub-group analysis can be performed after severity stratification (i.e. FMA < 17).

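### For normally distributed data, the primary FMA-UE comparison rests on a 2-df TIME × GROUP test with baseline as an outcome level, not on one baseline-adjusted Exp–Ctrl contrast at a named time

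*Protocol article*

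**What the plan says.** Protocol article, Outcomes {12}: "The primary outcome of the study is the difference between the Exp group and Ctrl group in functional mobility of the UL". The measure is fixed in the next sentence: "It will be measured using the Fugl-Meyer Assessment Scale for Upper Extremity (FMA-UE"). No time point is attached. Plans for assessment and collection of outcomes {18a} lists T0, T1 (after 3 weeks of treatment) and T2 (7 weeks from baseline) without ranking T1 and T2.

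Statistical methods for primary and secondary outcomes {20a}: parametric data get a 3 × 2 "mixed model ANOVA considering time" and group as within and between factors, at α = 0.05. Baseline is thus a level of the within factor ("TIME: T0 vs T1 vs T2"), and no covariate is mentioned. The follow-on rule is: "Each significant interaction (TIME × GROUP) will be further explored with the Bonferroni post hoc correction". Which comparisons are meant, and how many, is not said.

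This applies only to data judged normal. For other data the rule is: "Nonparametric data will be investigated with Friedman’s test and, if *p* < 0.05, with Wilcoxon test such as post hoc".

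**The concern.** The outcome is one between-group difference, but the stated test asks something broader: whether the two arms' profiles differ in any way across three visits. A significant 2-df interaction does not say at which visit the arms differ or by how much. That has to come from post hoc tests, which are reached only through the interaction and then pay a Bonferroni penalty. A within-arm post hoc would not compare the arms at all.

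Baseline FMA-UE is measured in every patient but enters only as a response. In an analysis of change it is therefore subtracted with a fixed slope of 1 instead of being adjusted for with an estimated slope. With 32 patients in total, two things are at stake: a clear estimate of the effect, and power at the step that supports the conclusion.

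**Working it through.** **Plan's own figure.** Sample size {14} gives 32 patients at 80% power, with no effect size, SD, correlation or named test. It can be neither reproduced nor refuted. It fits a two-sided two-group t test at 16 per arm with a standardised difference of about 1.02. It also fits a 2 × 3 interaction with f = 0.15 and correlation 0.8. The test behind it cannot be identified.

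**Inputs.** From the article: N = 32, two arms, three visits, α = 0.05. Assumed: 1:1 allocation (m = 16 per arm), unit SD, compound symmetry with between-visit correlation ρ from 0.7 to 0.95, and three Bonferroni comparisons. The only related figure in the article is the test–retest ICC of 0.97 for the FMA-UE motor score (Clinical and kinematic assessment), which points to a high ρ.

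**Step 1, reference.** ANCOVA at T1 has noncentrality λ = m·d²/(2(1−ρ²)) on 1 and 29 df. Power of 80% needs λ = 8.40, so d = √(8.40·2(1−ρ²)/16): 0.73 at ρ = 0.7 and 0.32 at ρ = 0.95.

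**Step 2, change from baseline at T1.** The variance is 2(1−ρ) against 1−ρ² for ANCOVA, a ratio of 2/(1+ρ). That is 2/1.7 = 1.18 at ρ = 0.7 and 2/1.95 = 1.03 at ρ = 0.95. Power as a single test at 0.05 is 73% to 79%, against 80%.

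**Step 3, omnibus interaction.** λ = (m/2)·Σ(d_t − d̄)²/(1−ρ) on 2 and 60 df. For effects (0, d, d) or (0, d, 0) the sum is (2/3)d². For (0, d, d/2) it is (1/2)d². Substituting step 1 gives λ = (2/3)(1+ρ)·8.40 or (1/2)(1+ρ)·8.40.

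| ρ | λ, effect kept or lost at T2 | power | λ, half kept | power |
|---|---|---|---|---|
| 0.7 | 9.52 | 77.3% | 7.14 | 64.1% |
| 0.8 | 10.08 | 79.8% | 7.56 | 66.8% |
| 0.9 | 10.64 | 82.0% | 7.98 | 69.3% |
| 0.95 | 10.92 | 83.1% | 8.19 | 70.5% |

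Allowing for chance baseline imbalance in the ANCOVA standard error raises d slightly (0.74 to 0.33). The interaction then has 79–84% and 66–72%.

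**Step 4, full route to a T1 statement.** This was simulated with 20,000 trials per cell: a significant interaction, then a T1 post hoc at 0.05/3, with d set as in the refined version of step 3. Correlations ran from 0.5 to 0.95, both compound-symmetric and decaying with time.
- Post hoc on change scores: about 48–65% (56–65% under compound symmetry with ρ of 0.7 to 0.95).
- Post hoc on raw T1 scores: about 5–45%.
- ANCOVA: 80% by construction, and ahead in every scenario.

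**Step 5, alternative target.** For the baseline-adjusted mean of T1 and T2 the residual variance is (1+ρ)/2 − ρ², so λ = c²·8.40·2(1+ρ)/(1+2ρ), with c = 1, 0.75 or 0.5 for an effect kept, half kept or lost at T2. Over ρ of 0.7 to 0.95, power is 90–92% if kept, 68–71% if half kept and under 40% if lost.

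**The case against.** The strongest defence is that a mixed-ANOVA interaction is a valid test of differential change, and that it is not weak where the correlation is high. With ρ above about 0.75 to 0.8, compound symmetry and an effect fully kept or fully lost at T2, it is level with or slightly ahead of ANCOVA at T1. That stands. A reader might infer that ANCOVA at T1 always has more power than the planned test; step 3 does not support this, and the article gives no effect shape that would decide it.

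Other stronger readings also fail:
- **Baseline imbalance is left uncorrected.** Not for the interaction: T0 is a level of TIME, so a constant offset between arms cancels. What remains is the fixed slope of 1, whose cost is small at high ρ. Recruitment {15} speaks only of demographic imbalance; Interim analyses {21b} is where clinical characteristics and upper-limb severity appear.
- **Patients missing a visit are dropped.** Section {20c} plans multiple imputation.
- **The plan compares raw T1 scores.** It does not say so. The contrasts and their number may be set in an analysis plan that is not shown, so the lowest powers in step 4 are conditional on that reading.
- **T1 is the right primary time.** The article names none, and the choice belongs to the investigators.

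An ANOVA also does not prevent reporting an estimate with a confidence interval. But {20a} does not single out one contrast to be estimated, so this only partly answers the point.

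**Conclusion.** The point holds in a limited form. When FMA-UE is treated as normal, the stated primary test is a 2-df interaction that does not directly estimate the single between-group difference defined as the outcome, and no primary time is named. Against the omnibus test alone, the power gain from a T1 ANCOVA depends on the effect shape: roughly 9 to 16 points if half the effect persists at T2, and between 3 points better and 3 points worse if it is fully kept or lost. Against the complete gated route to a T1 conclusion, the single contrast is better in every case tried, by about 15 to 32 points with change-score post hocs.

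These sizes rest on the assumed 1:1 allocation, correlations, effect shapes and three comparisons. The mismatch between outcome and test does not. It should be changed, but the planned test is not invalid.

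**What to change.** Name one primary time point: T1, or the mean of T1 and T2 if a lasting effect is the question. Step 5 shows the trade-off. The mean gains power if the effect is sustained and loses it if the effect fades.

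Make the primary analysis one Exp–Ctrl contrast in FMA-UE at that time, with baseline FMA-UE as covariate, two-sided α = 0.05, reported as an adjusted difference with a 95% CI. Keep the other time point and the 3 × 2 interaction as secondary.

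The cost is a change of analysis wording, one degree of freedom for the covariate, and secondary status for the other time point. No new data are needed. The change should be fixed without reference to outcome data by arm, including the interim results at 20 patients.

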## Trial design {8}

A randomised, parallel groups, double-blind, two-arms, sham-controlled trial will be implemented to investigate the effects of the PPC-M1 PAS in add-on to RAT. Neurologists, PM&R, engineers, psychologists and physiotherapists were involved in the study design. No patient or public participation was foreseen.

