## Discussion

The objective of the current study protocol is to test the effects of a PPC-M1 PAS in add-on to 15 consecutive sessions of RAT on motor function of the upper limb in chronic stroke via a RCT with a multimodal investigation (clinical, kinematic and neurophysiological). In line with the aim of the current study protocol, Tang et al. in their meta-analysis reported how using high-frequency TMS on the ipsilateral hemisphere is beneficial for motor function, hand strength and hand dexterity in patients diagnosed with sub-acute stroke [29]. Similarly, a network meta-analysis on non-conventional therapies for motor recovery after a stroke reported the high-frequency repetitive transcranial magnetic stimulation as one of the most effective treatments [30]. Similarly, to our protocol, a very recent study tested the combination of another form of non-invasive brain stimulation (dual-tDCS) combined with robot-assisted therapy in chronic stroke finding a positive effect on motor functions in the subgroup of patients with severe cortico-spinal damage treated with real stimulation with respect to the control [31]. Based on the abovementioned scientific evidence, we expect that the stimulation of the central nervous system by the augmented feedback generated by robot-assisted therapy, during the neuromodulation window induced by PAS, can promote a cortical reorganisation which in turn results in a clinical improvement. Therefore, the combination of the two approaches should generate a boost effect on functional motor recovery of UL.

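### Correlations and regressions between clinical, kinematic and neurophysiological data carry no arm term, so a treatment effect on both measures can induce or distort the association

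*Protocol article*

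**What the plan says.** The section on statistical methods for primary and secondary outcomes {20a} names the association analyses by method: "Correlations (Pearson for normal distributed data or Spearman for non-normal distributed data) and regression analysis will be performed between clinical, kinematic and neurophysiological data". It gives their purpose as "to investigate casual and causal interaction respectively".

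In the same section the arm factor appears once, in the mixed ANOVA, with time and "group allocation (GROUP: Real vs Ctrl) as within and between factors, respectively". The only split of the sample that the section mentions is by severity. It does not say whether the correlations use raw values or changes, or at which visit.

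The outcomes section {12} sets up the secondary measures as between-group contrasts: "Secondly, we will investigate clinical, kinematic and neurophysiological changes between the two groups using". The objectives {7} assume that PAS acts directly on cortical plasticity. The Discussion expects that robot-generated feedback, given in the window that PAS opens, "can promote a cortical reorganisation which in turn results in a clinical improvement".

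**The concern.** A plain Pearson or Spearman coefficient takes no covariate. A regression of one outcome on another without GROUP tests the same thing as Pearson. If all patients are analysed together and real stimulation shifts both variables, the arm is a common cause of both. The two arms then form two clouds of points displaced along both axes, and the pooled data are correlated by that displacement. This happens even if patients whose cortex changed more recovered no better than others in their own arm. If a within-arm association does exist, pooling distorts its size.

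The distortion is largest in the result that the trial hopes for, a benefit on both the TMS-EEG and the clinical measures. A significant pooled coefficient could then be read as patient-level support for the mechanism in the Discussion, although it restates two between-arm differences. The declared causal purpose of the regression makes that reading more likely.

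**Working it through.** **The plan's own figure.** The sample size section {14} says "considering 80% power and a 95% CI, 32 patients would be needed for necessary sample size". It gives no effect size or SD, so 32 cannot be reproduced. Solving backwards for 16 per arm, two-sided 0.05 and 80% power, the normal approximation n per arm = 2(1.96 + 0.84)²/d² gives d of about 0.99. The t-test gives d = 1.02. This serves only as a scale for the shifts below. The protocol does not claim it.

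**Inputs.**
- N = 32 in two parallel arms (sections {14} and {8}). A 1:1 split, 16 per arm, is assumed because no ratio is stated.
- Alpha 0.05, which {20a} states for the ANOVA. Two-sided testing, and the same level for the correlations, are assumed.
- One value per patient for each measure, normally distributed, with zero correlation within each arm (assumed).
- Real PAS shifts the two measures by d1 and d2 within-arm SDs (assumed, over a range).

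**Formula.** With equal arms the arm indicator has variance 1/4. The pooled covariance is therefore d1·d2/4, the pooled variances are 1 + d1²/4 and 1 + d2²/4, and

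r = (d1·d2/4) / √[(1 + d1²/4)(1 + d2²/4)].

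Examples:
- d1 = d2 = 1: 0.25/1.25 = 0.20.
- d1 = d2 = 1.5: 0.5625/1.5625 = 0.36.
- d1 = 1.02, d2 = 0.5: 0.1275/√(1.2601 × 1.0625) = 0.11.

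**Rejection rates.** Simulation with 20,000 replicates. The adjusted column is the Pearson correlation partial on arm, with 29 df.

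| d1, d2 (SD) | Pooled r | Pearson | Spearman | Adjusted for arm |
|---|---|---|---|---|
| 0, 0 | 0 | 5.2% | 5.2% | 5.1% |
| 0.5, 0.5 | 0.06 | 6.1% | 6.1% | 5.0% |
| 0.8, 0.8 | 0.14 | 11.7% | 11.5% | 4.8% |
| 1.0, 1.0 | 0.20 | 20.2% | 20.6% | 5.2% |
| 1.02, 1.02 | 0.21 | 21.5% | 21.9% | 5.2% |
| 1.5, 1.5 | 0.36 | 58.0% | 60.6% | 5.1% |
| 1.02, 0.5 | 0.11 | 9.3% | 9.4% | 4.8% |
| 1.02, 0 | 0 | 4.7% | 4.8% | 4.7% |

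A separate run gave 57% for Pearson at 1.5 SD. A Pearson correlation computed inside a single arm of 16 rejects in about 5% of replicates at every setting.

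**The case against.** The strongest reply is that the protocol never says the arms are pooled. Plain coefficients computed separately in each arm fit the text and are free of the artefact, and the full protocol or analysis plan, not shown, may settle it. Part of this stands: pooling is the natural reading, not an explicit statement. But the methods are named, GROUP is attached to the ANOVA alone and no split by arm is given. As written, the text leads an analyst to the unadjusted version.

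The second reply is that the effect is often small, and this stands. It is negligible at 0.5 SD and absent if only one measure shifts. The sample size section gives no effect size and refers to work on cortical plasticity, so it does not support a shift of about 1 SD in clinical or kinematic measures. A correlation that exists in neither arm also requires zero within-arm correlation; otherwise pooling distorts an association that is already there.

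Third, regression can carry an arm term, and the text does not rule one out. That is true, but it does not state one either, and the correlations remain unadjusted in any case.

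A reader might infer three stronger points that the document does not support:
- That the correlations are the only planned link between TMS-EEG and clinical results. The same sentence also plans regression.
- That the three visits will be stacked as independent rows. This is nowhere planned.
- That every correlation is affected. Baseline correlations precede treatment and carry no treatment-induced shift.

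**Conclusion.** The point holds as a conditional weakness of a secondary analysis. If both arms are analysed together and real PAS shifts both measures, unadjusted associations of post-treatment data mix the between-arm effect with the patient-level association.

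With 16 per arm and no within-arm correlation, the chance of a significant coefficient rises from the nominal 5% to about 20% when both measures shift by 1 SD. It reaches 57% to 58% at 1.5 SD, but stays at 6% to 12% for shifts of 0.5 to 0.8 SD. These figures rest on assumed shifts, an assumed 1:1 split and the plain reading of the text. They do not predict what this trial will find.

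The remedy is inexpensive, so the change is worth making. The between-group comparison of FMA-UE, the primary outcome, is not touched.

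**What to change.** In section {20a}, state that:
- correlations involving T1 or T2 data use one change score per patient, T1 minus T0 and T2 minus T0 analysed separately, and are partial Pearson or partial Spearman correlations adjusted for GROUP;
- GROUP is a covariate in every regression of one post-treatment outcome on another;
- correlations among baseline (T0) measures may stay unadjusted.

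The cost is one or two sentences of analysis wording and one degree of freedom per analysis (29 in place of 30 with 32 patients). No new data are needed. Adjusting for arm removes the artefact described here, but it does not by itself justify a causal reading of an association between two outcomes.
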